#### Description of the Intervention (Schedule of Visits)

Visit 1 (screening, within 1 month from initial diagnosis)

Patients will be informed about the study. Once patients agree with the inclusion in the study, we will evaluate the inclusion and exclusion criteria. Those patients who meet all the inclusion criteria and none of the exclusion criteria will be finally included in the study. In this visit, patient-related, tumor-related, and pancreatic function and treatment-related variables will be recorded, and quality of life questionnaire will be administered. The researcher will record weight, height, BMI, and unplanned WL % for the last 6 months.

Each patient's baseline nutrition status will be evaluated using the MNA score prior to starting chemotherapy. Patients will be classified as in the group with no nutritional risk, at risk of malnutrition, or malnourished.

Nutritional parameters and pancreatic function will be evaluated through blood tests and a fecal test.

Visit 2 (3 months after the first dose of planned chemotherapy)

The researcher will record in the CRF the planned chemotherapy, schedule, doses, dose reduction, and any adverse event^1^. The same variables recorded at Visit 1 will be checked again.

Check-up 3 (end of the study, 6 months)

The researcher will record in the CRF the OS and time until progression.

#### Medication of the Study

The study is of observational nature, so a pre-planned treatment is not considered. However, the use of pancreatic enzyme replacement treatment will be recorded as well as data regarding the employed chemotherapy regimen.

#### Statistical Analysis

The STROBE guidelines for observational studies will be followed to report our findings^2^. Descriptive statistics (including mean, standard deviation, median, range, frequency, and percent) will be calculated to characterize the study cohort.

Chemotherapy dosing over the first 12 weeks of therapy (i.e., percent chemotherapy received in the first 12 weeks, as defined above) will be compared between well-nourished and malnourished patients. Two-sample *t*-tests/Wilcoxon rank-sum tests will be used for MNA comparisons of mean/median percent chemotherapy received, for all patients and stratified by risk for toxicity. Two-sample *t* tests/Wilcoxon rank-sum tests and chi-square tests/Fisher's exact tests will be used, as appropriate, to compare malnutrition status between groups based on MNA, on demographic/clinical characteristics of interest.

Multivariable logistic regression analysis will be used to estimate the independent effect of malnutrition status on percent chemotherapy received (<80% chemotherapy received vs. 80% chemotherapy received; binary end point), after controlling for demographic and clinical characteristics (age, sex, race, ECOG status, tumor site, tumor stage, PEI, and DM). The demographic and clinical variables included in the final model will be chosen using a forward-stepwise method. Similarly, multivariable linear regression analysis will be used to estimate the independent effect of nutritional status on mean percent chemotherapy received (i.e., continuous endpoint), after controlling for demographic and clinical characteristics. All *p* values are two-sided with statistical significance evaluated at the 0.05 alpha level. Ninety-five percent confidence intervals (CIs) will be calculated to assess the precision of the obtained estimates (for odds ratios/beta estimates). The Kaplan–Meier method will be used to estimate OS and progression-free survival (PFS). The log-rank test will be used to compare OS and PFS between well-nourished patients and malnourished patients. Greenwood's formula will be used to calculate 95% CIs for Kaplan–Meier survival estimates. The frequency and percentage of missing values for each variable will be collected, analyzed, and reported (missing value analysis). All data will be anonymous once data collection is completed, respecting the confidentiality of the subjects participating, in accordance with data protection laws. All analyses will be performed in STATA 14 (Statacorp LLC, Texas).

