Cachexia and malnutrition not only represent symptoms of the disease but also are important factors having a significant impact on the outcome of PDAC patients (9). A low value of fecal elastase-1, depicting impaired exocrine pancreatic function and contributing to cachexia, has been reported to strongly correlate with poor survival in advanced PDAC patients (10). However, cachexia and impaired nutritional status might also affect the tolerance and response to medical treatments such as chemotherapy. This is particularly important in PDAC; not more than 20% of patients are eligible for the resection at the time of the diagnosis (3), while the rest might have an indication for chemotherapy. In this setting, while Gemcitabine mono-chemotherapy has for a long time been the standard treatment for unresectable PDAC with relatively poor effect represented by a median overall survival (OS) around 6 months (11), intensified regimens, such as the combination of 5-fluorouracil, leucovorin, irinotecan, and oxaliplatin (FOLFIRINOX), or the addition of Nab-Paclitaxel to gemcitabine, are nowadays more frequently used, with substantially improved survival (12–17). However, due to their side effects, particularly encountered in FOLFIRINOX, intensified regimens can be less tolerable, leading to dose reduction or therapy discontinuation (13–15), which makes their use limited to the patients with ECOG status of 0, 1, and 2 (15, 16). For patients with ECOG of 3 or higher, the large majority of experts recommend best supportive care (18).

Considering this, it is even more important to assess the impact of the nutritional status in patients with advanced PDAC in order to identify sub-groups at a higher risk of side effects and treatment discontinuation. If timely identified, these patients could be approached and treated accordingly, in order to increase their capacity to complete the planned therapy and therefore possibly improve its efficacy. Studies so far conducted to address this important issue have been too few and limited in terms of parameters evaluated as well as outcomes observed and often did not use standardized measures. Hence, evidence is sparse and heterogeneous.

We, therefore, designed a multicenter prospective study in order to assess the impact of patient's nutritional status on the clinical course of advanced PDAC patients receiving chemotherapy.

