## Methods

### Study Design

The PAncreatic Cancer MAlnutrition and exocrine pancreatic INsufficiency in the course of chemotherapy in unresectable pancreatic cancer (PAC-MAIN) study is a non-profit, international, multicenter, prospective, observational, cohort study evaluating the effect of the nutritional status and pancreatic exocrine function on the main outcomes of patients with advanced PDAC. The study will be carried out in Russia, Turkey, Serbia, Romania, Italy, and Spain as a part of the Pancreas 2000 Educational Program. Pancreas 2000 is a post-graduate educational program that prepares young gastroenterologists, surgeons, radiologists, and other physicians for specialization in Pancreatology (19).

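### The fixed covariate list for the malnutrition effect leaves out planned regimen and centre/country, so the adjusted estimate can be confounded by regimen in either direction

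*Protocol article*

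**What the plan says.** All references are to the Protocol article.

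- **Statistical Analysis** specifies a logistic model (80% threshold) for the independent effect of malnutrition, "after controlling for demographic and clinical characteristics (age, sex, race, ECOG status, tumor site, tumor stage, PEI, and DM". A linear model for mean percent received is adjusted in a similar way.
- The same section adds: "The demographic and clinical variables included in the final model will be chosen using a forward-stepwise method".
- The main comparison there is an unadjusted t-test or Wilcoxon test, "for all patients and stratified by risk for toxicity". The article does not define that risk, and it is not among the listed variables.
- **Background** states that "intensified regimens can be less tolerable, leading to dose reduction or therapy discontinuation", and adds, of the same regimens, "which makes their use limited to the patients with ECOG status of 0, 1, and 2".
- **Medication of the Study** states: "The study is of observational nature, so a pre-planned treatment is not considered". It also says that "data regarding the employed chemotherapy regimen" will be recorded. The treatment-related items under Variables include the planned protocol.
- **Outcomes** defines percent of standard dose against the published schedule of the patient's own regimen, averaged over its drugs.
- **Study Design**: "The study will be carried out in Russia, Turkey, Serbia, Romania, Italy, and Spain".

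**The concern.** The covariate list is stated in full, so this is a choice made in the text rather than a detail left for later. An analysis that follows it will not contain regimen, because stepwise selection works only within the list.

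By the document's own account, regimen affects the outcome. The outcome does not remove that dependence: each patient is scored against the standard dose of his or her own regimen, so 80% of a mild regimen and 80% of an intensified one count the same, although the second is harder to deliver. Clinicians choose the regimen freely. If the choice differs by nutritional status for reasons the listed covariates do not capture, the estimate labelled as the independent effect of malnutrition also contains a regimen effect. A null result could then hide a real deficit, or a positive one could be inflated.

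Centre or country is a secondary matter. With treatment unfixed across six countries, centre could be related to both nutritional mix and dosing.

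**Working it through.** **1. The plan's own figures.** Power Size Calculation gives 93, 163 and 356 per group for 70% versus 50%, 55% and 60%, with type I error 0.05 and type II error 0.20. The two-proportion formula is

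n = [1.960·√(2·p̄·(1−p̄)) + 0.842·√(p1(1−p1) + p2(1−p2))]² / (p1−p2)².

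For 70% versus 50%: (1.960·√0.48 + 0.842·√0.46)² / 0.04 = 93. The other two give 163 and 356. All three reproduce, so the point does not rest on an arithmetic error.

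**2. Size of a regimen shift (assumed inputs).** The documents give neither the regimen mix by nutritional group nor the effect of regimen on percent dose. Let g be the number of points by which an intensified regimen lowers percent dose, and let D be the share of well-nourished patients on such a regimen minus the share of malnourished patients. Then

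apparent crude deficit = true deficit − g × D.

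With D = 0.30 (for example 60% versus 30%):

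- g = 10: shift 10 × 0.30 = 3 points
- g = 15: shift 15 × 0.30 = 4.5 points
- g = 20: shift 20 × 0.30 = 6 points

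This is 30 to 60% of a 10-point effect, 20 to 40% of a 15-point effect and 15 to 30% of a 20-point effect. With D = −0.30 the shift has the same size and the opposite sign. With D = 0 there is none.

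**3. Apparent deficits for the plan's three scenarios.** Power for D = +0.30 comes from the formula in step 1, solved for power at the stated n, with 70% in the well-nourished group and 70% minus the apparent deficit in the malnourished group.

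| True deficit | n per group | D = +0.30, g = 10 to 20 | Power at that n | D = −0.30, g = 10 to 20 |
|---|---|---|---|---|
| 20 | 93 | 17 to 14 | 67% to 51% | 23 to 26 |
| 15 | 163 | 12 to 9 | 62% to 40% | 18 to 21 |
| 10 | 356 | 7 to 4 | 51% to 21% | 13 to 16 |

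Without any shift, power is 80% in each row.

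**4. What these numbers cover.** They describe the crude difference. Adjustment for ECOG, age and stage would remove some of the shift, by an amount the documents do not allow one to calculate.

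**5. Does ECOG stand in for regimen?** Patients with ECOG 3 or higher are excluded (Patients). Everyone enrolled is therefore within the ECOG range that the Background gives for intensified regimens. ECOG 0, 1 or 2 may still predict the choice, but it does not determine it, and the stepwise step may not retain ECOG.

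**The case against.** The strongest case against has four parts.

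- **Mediation.** Nutritional status is assessed before chemotherapy starts. If poor nutrition leads clinicians to choose a milder regimen, regimen lies partly on the causal path. The hypothesis of an adverse impact on clinical course can be read as a total effect, and leaving regimen out is then defensible. This stands. It is why both estimates are needed, and why a regimen-adjusted model cannot simply replace the other.
- **No stated link between regimen and nutrition.** The Background ties regimen choice only to ECOG, and ECOG is a candidate covariate. This stands in part: confounding is possible but not shown, and ECOG is an incomplete proxy.
- **Centre.** Nothing in the document says that dosing practice or nutritional mix differs by centre. This stands. The centre term is a cheap precaution suggested by the six-country design. A reader might infer that the standard errors are wrong, but no cluster sizes or intraclass correlation are given to support that.
- **Handled elsewhere.** Outcomes promises to examine the association of all recorded variables with the outcomes, and lists factors associated with percent received as a secondary outcome. The crude tests are stratified by toxicity risk. None of this puts regimen into the adjusted malnutrition model.

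A reader might also infer that the adjusted model must become primary, or that the toxicity-risk strata should be replaced by regimen. The first is a trade-off, since adjusted models are already planned. The second guesses at a term whose definition may sit in the full protocol.

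**Conclusion.** The point holds as a possible, two-directional bias. The explicit list omits a recorded variable that the document itself names as a cause of dose reduction, and no other planned analysis brings it into the malnutrition model. The plan also does not say whether a total effect or an effect at a given regimen is wanted.

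A reader might go further and conclude that the estimate is confounded and that a true harm will be masked. The document does not support that: it gives no regimen mix by nutritional status, and masking follows only if well-nourished patients receive intensified regimens more often. The opposite pattern would exaggerate the deficit.

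The size, 3 to 6 points of crude difference, rests on an assumed 30-point difference in shares and an assumed 10 to 20 point regimen gap. To the extent that nutritional status itself drives regimen choice, that shift is part of the total effect and not bias.

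**What to change.** In both the linear and the logistic model of Statistical Analysis:

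1. Force in centre or country, as a fixed effect or a random intercept, outside the forward-stepwise selection.
2. Report the malnutrition effect twice: without regimen (total effect) and with planned regimen forced in (effect not acting through regimen choice).
3. State in advance which of the two is the target.

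Forcing matters, because a variable merely added to the candidate list could be dropped again.

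The cost is a change of wording and a few degrees of freedom. Regimen is already recorded, and centre is known in a multicentre database. The regimen-adjusted estimate excludes any effect mediated by regimen choice, which is the reason to show it beside the other.

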## Background

Pancreatic ductal adenocarcinoma (PDAC) represents one of the most lethal malignancies nowadays (1), with an age-standardized incidence rate of 4.8 and age-standardized mortality of 4.4 per 100,000 people worldwide. PDAC accounts for the majority of cases of pancreatic neoplasms (2). Diagnostic and therapeutic advancements led to a decrease in mortality of the most cancer types during the last decades; however, PDAC mortality still almost equals the incidence (1), with 5-year survival lower than 10% in the United States (3). The fact that most PDAC patients remain asymptomatic until advanced stages of the disease, as well as the aggressive biological behavior of this tumor and the absence of an effective screening method, largely contribute to these results. However, taking into account that more than 450,000 persons each year are diagnosed with PDAC (1) representing significant healthcare and socioeconomic burden, there is a substantial need for improvement in the diagnostics and therapy in order to prolong survival.

A profound weight loss is one of the early symptoms of PDAC that can precede the diagnosis by months (4). Cachexia, as a symptom and consequence of the disease course, is present in many cancer types, especially in the late stages. Fearon et al. (5) described it as a multifactorial syndrome defined by an ongoing loss of skeletal muscle mass (with or without loss of fat mass) that cannot be completely reversed by conventional nutritional support and leads to progressive functional impairment. In addition to changes such as skeletal muscle wasting or loss of adipose tissue, cachexia is associated with changes in numerous nutritional parameters (6). Among the mechanisms determining the tumor-induced cachexia, the breakdown of molecules due to increased catabolism and inflammation are considered very important (7). Moreover, it has been recently reported that altered pancreatic exocrine function can additionally contribute to cachexia in pancreatic cancer by driving adipose tissue wasting (8).

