### Hypothesis

We hypothesize that malnutrition has an adverse impact on the clinical course of patients with advanced PDAC treated with chemotherapy.

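### Forward-stepwise selection decides whether the adjusted malnutrition coefficient is conditional on ECOG, so what it estimates is not fixed in advance

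*Protocol article*

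**What the plan says.** The Hypothesis section states that "malnutrition has an adverse impact on the clinical course of patients with advanced PDAC treated with chemotherapy". The multivariable part of Statistical Analysis turns this into two models. The logistic model, on receipt of less than 80% of chemotherapy, is meant to "estimate the independent effect of malnutrition status on percent chemotherapy received", "after controlling for demographic and clinical characteristics (age, sex, race, ECOG status, tumor site, tumor stage, PEI, and DM". The linear model is introduced as similar and is meant to "estimate the independent effect of nutritional status on mean percent chemotherapy received". Between the two stands the selection rule: "The demographic and clinical variables included in the final model will be chosen using a forward-stepwise method". ECOG is thus a candidate covariate that may or may not be in the final model.

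The same section also plans t-tests or Wilcoxon tests of percent chemotherapy received by MNA group, in all patients and by toxicity risk, with no covariates.

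Two Background statements bear on what ECOG represents. Cachexia is described as muscle loss that "cannot be completely reversed by conventional nutritional support and leads to progressive functional impairment". On intensified regimens, limited tolerability is given as the reason "which makes their use limited to the patients with ECOG status of 0, 1, and 2". Under Variables and the schedule of visits, MNA and ECOG are both collected at Visit 1. Patients with ECOG 3 or higher are excluded, so the cohort spans ECOG 0 to 2.

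**The concern.** A covariate that may lie between exposure and outcome is listed with age, sex and tumor stage, and an algorithm decides whether it enters. If malnourished patients receive less chemotherapy partly because they are weaker, a model containing ECOG leaves that part out of the malnutrition coefficient, and a model without ECOG keeps it in. If instead ECOG mainly reflects disease burden that also drives malnutrition, the model without ECOG is the misleading one. The plan does not say which reading it intends.

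Stepwise selection adds to the difficulty. ECOG is most likely to enter when it predicts dose strongly, which is also when mediation or confounding through it can be largest. It may enter the linear model and not the dichotomised one, or the reverse, and the two coefficients would then answer different questions under the same label.

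The stake is interpretation. The Background's purpose is to find malnourished patients who could be helped to complete treatment. A near-null coefficient from a model that happened to select ECOG could be reported as little independent effect of malnutrition, with no confounder-adjusted figure without ECOG beside it.

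**Working it through.** **1. The plan's own figures.** The planned sizes come from a two-proportion formula: n = [1.96·√(2p̄(1−p̄)) + 0.8416·√(p₁(1−p₁)+p₂(1−p₂))]² / (p₁−p₂)². For 70% against 50%: [1.96·√0.48 + 0.8416·√0.46]² / 0.04 = 93. Against 55% it gives 163 and against 60% it gives 356, all as stated. These sizes concern the crude comparison and do not involve ECOG. They serve here only to set the scale of effect (10 to 20 points).

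**2. What can be computed from the document.** It gives no ECOG distribution, no ECOG effect on dose and no ECOG–MNA association. Steps 3 to 5 are therefore illustrations with assumed inputs. Steps 3 and 4 reduce ECOG to grade 2 against 0–1, with b the effect of ECOG 2 on percent dose (−10 or −20 points).

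**3. ECOG purely a mediator.** Assume a total effect T = −20 points, ECOG 2 in 20% of well-nourished patients, and an excess a of 15 to 45 percentage points in malnourished patients. The ECOG-adjusted coefficient is T − a·b.
- Smallest case: −20 − (0.15)(−10) = −18.5, so 1.5/20 = 7.5% is removed.
- Largest case: −20 − (0.45)(−20) = −11.0, so 9/20 = 45% is removed.

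**4. ECOG purely a confounder.** Assume a true effect of −15, ECOG 2 in 35% of patients, and malnutrition in 35% of those with ECOG 0–1 and in 35% + a of those with ECOG 2. Omitting ECOG adds b·[P(ECOG 2 | malnourished) − P(ECOG 2 | well-nourished)].
- a = 0.15, b = −10: 0.175/0.4025 − 0.175/0.5975 = 0.435 − 0.293 = 0.142. The bias is −1.4 and the estimate −16.4.
- a = 0.45, b = −20: 0.28/0.5075 − 0.07/0.4925 = 0.552 − 0.142 = 0.410. The bias is −8.2 and the estimate −23.2.

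Simulated linear models (200,000 patients per scenario, residual SD 25) agree up to sampling error:

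| a | b | Mediator: with ECOG | Share removed | Confounder: without ECOG | Confounder: with ECOG |
|---|---|---|---|---|---|
| 0.15 | −10 | −18.4 | 7% | −16.4 | −15.0 |
| 0.15 | −20 | −17.1 | 15% | −18.1 | −15.3 |
| 0.30 | −10 | −16.9 | 15% | −17.7 | −14.9 |
| 0.30 | −20 | −13.9 | 30% | −20.4 | −14.9 |
| 0.45 | −10 | −15.4 | 23% | −19.1 | −15.0 |
| 0.45 | −20 | −11.1 | 45% | −23.0 | −14.9 |

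**5. Why the ECOG-adjusted figure is not a clean direct effect.** A further simulation (1,000,000 patients per scenario) let disease burden affect both ECOG and dose, with stage as a noisy proxy for burden. Assumed inputs: direct effect −6 points, ECOG effect −6 or −10 points per grade, malnutrition shifting latent function by 0.3 to 0.9 SD, residual SD 20. With burden unrelated to malnutrition, the total effect was −7.0 to −11.4, but the model with ECOG returned −5.4 to −5.8 and not −6. Among patients of equal ECOG, malnutrition and residual burden become associated, which pulls the coefficient slightly towards zero.

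**The case against.** The strongest defence is that the plan asks a legitimate conditional question: does nutritional status add information beyond performance status and the other listed factors? The Aims speak of association, and the Background wants to identify higher-risk subgroups. ECOG also governs access to intensified regimens, which is a reason to adjust for it. If it is a confounder, the adjusted estimate is about right and the estimate without it is too large. This stands: including ECOG is not in itself an error, and simply dropping it would not be an improvement.

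A reader might be tempted by three stronger readings, which the document does not support:
- That the document itself makes ECOG a consequence of cachexia. It speaks of functional impairment and does not name ECOG. Cachexia is also recorded as a variable separate from the MNA categories that define the exposure.
- That no estimate without ECOG is planned. The crude MNA comparison of percent chemotherapy received has no covariates, and the log-rank tests for OS and PFS are unadjusted too. Only a confounder-adjusted estimate without ECOG is absent.
- That part of the effect is removed. Stepwise selection may leave ECOG out, and measurement at the same visit does not settle the order. The Background does say that weight loss can precede diagnosis by months, so nutritional decline before baseline ECOG is plausible, but it is not shown.

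It can also be said that a model with and without one covariate is normally left to a statistical analysis plan. That would answer a complaint about a missing sensitivity analysis. It does not answer this one, because the article itself fixes the candidate list, the selection rule and the label given to the result.

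**Conclusion.** The point holds in a limited form. The plan gives one causal-sounding label to a coefficient whose meaning depends on whether an algorithm admits ECOG, and the two endpoints may be treated differently. This is worth changing. It does not undermine the crude comparison, nor does it show that the planned adjusted estimate is biased in a known direction.

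Under the assumed inputs, adjustment removes about 7% to 45% of a 20-point effect if ECOG is purely a mediator. Omission overstates a 15-point effect by about 1.4 to 8 points if ECOG is purely a confounder. The truth may be a mixture, and other assumptions give other ranges: in the scenarios of step 5, 17% (1 − 5.8/7.0) to 53% (1 − 5.4/11.4) of the total effect is removed. These figures show that either estimate alone can mislead; they do not estimate what will happen in this cohort. That ECOG is partly downstream of malnutrition remains an inference.

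**What to change.** In the multivariable part of Statistical Analysis, replace the stepwise choice with two pre-specified models for each endpoint (linear and logistic):
1. Malnutrition status with age, sex, race, tumor site, tumor stage, PEI and DM.
2. The same covariates with ECOG forced in.

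Report both malnutrition estimates with 95% CIs, beside the crude comparison. Describe the second as the association conditional on performance status, not as a direct effect. State in advance that absence of an impact of malnutrition will not be concluded from the ECOG-adjusted model alone. When reading the two logistic results together, bear in mind that an odds ratio can shift when a predictor of outcome is added even without confounding or mediation; the linear pair is the cleaner comparison.

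The cost is one extra model per endpoint, a sentence or two of interpretation, and two adjusted estimates to explain where there would have been one. No new data are needed, and the change takes no side on whether ECOG is a mediator or a confounder.

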### Aims

To investigate the association between the nutritional status and pancreatic exocrine function and the clinical outcomes of patients with advanced PDAC.

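### Forward-stepwise choice among the eight listed covariates can omit real confounders and tends to make the 95% CI for the adjusted malnutrition effect too narrow

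*Protocol article*

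**What the plan says.** All references are to the protocol article. Statistical Analysis sets out the adjusted analysis: "Multivariable logistic regression analysis will be used to estimate the independent effect of malnutrition status on percent chemotherapy received", with the outcome split at 80%. The covariates to be controlled for are "age, sex, race, ECOG status, tumor site, tumor stage, PEI, and DM". The next sentence makes the list provisional: "The demographic and clinical variables included in the final model will be chosen using a forward-stepwise method". A linear model for the continuous percentage follows and is introduced as similar, so I read the same rule as applying to it. The section gives no entry threshold, forces no covariate in, and plans ordinary 95% CIs for the odds ratios and regression coefficients.

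Two other places bear on this. PEI is more than a nuisance covariate: the Aims read "To investigate the association between the nutritional status and pancreatic exocrine function and the clinical outcomes of patients with advanced PDAC", and Study Design describes the cohort as "evaluating the effect of the nutritional status and pancreatic exocrine function on the main outcomes of patients with advanced PDAC". Background describes low fecal elastase as "depicting impaired exocrine pancreatic function and contributing to cachexia" and reports that it correlates with poor survival.

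**The concern.** The models are meant to estimate the effect of one named exposure, not to predict. The design offers no other protection against confounding: "The study is of observational nature, so a pre-planned treatment is not considered", and the group comparisons described before the regression are unadjusted. Regression is therefore the main stated control.

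Forward selection asks whether a covariate reaches significance as a predictor of the outcome. Whether a covariate confounds depends also on its link with the exposure. A moderate confounder, clearly tied to malnutrition and modestly tied to dose delivered, can fail the test at the planned sample sizes and be left out. Its confounding then stays in the malnutrition coefficient. The standard error is also computed as if the model had been fixed in advance.

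PEI shows what is at stake. On the article's own account it contributes to cachexia and goes with worse outcome, so it is a plausible common cause of malnutrition and poor treatment delivery. The rule may nevertheless remove it.

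**Working it through.** **Sample sizes.** Power Size Calculation gives 93, 163 and 356 per group for 70% against 50%, 55% and 60%, with alpha 0.05 and power 0.80. The two-proportion formula with pooled variance reproduces them:

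n = [1.960·√(2·p̄(1−p̄)) + 0.842·√(p1(1−p1)+p2(1−p2))]² / (p1−p2)²

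- 70 v 50: (1.358 + 0.571)² / 0.04 = 93.0, so 93
- 70 v 55: (1.342 + 0.569)² / 0.0225 = 162.3, so 163
- 70 v 60: (1.322 + 0.565)² / 0.01 = 355.9, so 356

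The totals used below are 2×93 = 186, 2×163 = 326 and 2×356 = 712.

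**Assumptions (none is in the article).** There are eight independent standard-normal candidates, four of them true confounders acting in the same direction. The true malnutrition effect is null, malnutrition is always in the model, and entry is at p<0.05. Each setting has 400 cohorts. In the logistic model each confounder acts on the outcome at 0.2 or 0.3 log-odds per SD and on exposure with coefficient 0.4, and about half the patients have the outcome event. In the linear model the effects are 0.10 or 0.15 SD on the outcome and 0.3 or 0.5 on exposure.

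**Logistic model**

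| N | Confounder effect | Stepwise coverage | Stepwise mean log-OR | Full-model coverage | A given true confounder retained |
|---|---|---|---|---|---|
| 186 | 0.2 | 80.7% | 0.242 | 94.8% | 19% |
| 186 | 0.3 | 77.0% | 0.261 | 95.5% | 40% |
| 326 | 0.2 | 80.5% | 0.182 | 94.8% | 36% |
| 326 | 0.3 | 83.5% | 0.114 | 95.3% | 69% |
| 712 | 0.2 | 81.5% | 0.104 | 94.3% | 61% |
| 712 | 0.3 | 90.7% | 0.027 | 93.8% | 93% |

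- *Bias.* The true OR is 1. At 186 patients the stepwise model gives exp(0.242) = 1.27 and exp(0.261) = 1.30 on average. The full model's mean log-OR lies between −0.013 and 0.017.
- *Width.* At 186 patients the mean stepwise model SE is 0.311 or 0.325, against an actual spread of 0.372 or 0.425. The ratios are 0.311/0.372 = 0.84 and 0.325/0.425 = 0.76, so the interval is 16-24% too short, in addition to being off-centre.
- *Simulation error.* √(0.80×0.20/400) = 2.0 points near 80% coverage and √(0.95×0.05/400) = 1.1 points near 95%. The gaps at 186 and 326 patients are far larger than this.

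**Linear model.** Stepwise coverage was 72-88% at 186, 74-88% at 326 and 78-94% at 712; the full model gave 94.8-95.5%. The lowest values come from the stronger exposure link (0.5).

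**Milder settings.** With about one third of patients in the smaller outcome class (logistic, 600 cohorts), stepwise coverage was 86.5% at 186 and 88.8% at 326, against 94.2% and 94.7% for the full model. A moderate linear set gave 86-88% and 88-89%, against 94-96%. Another linear set (800 cohorts per setting) gave 82-89% and 83-92%. One of its full-model results, 91.8%, is (95−91.8)/0.77 ≈ 4 simulation errors below nominal, so I use that set only for the favourable end of the range.

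**Sensitivity.** Entry at p<0.20 with 186 patients raised logistic coverage from 77.0% to 91.5%, and raised linear coverage in the harshest setting from 72.0% to 87.7%. With no true confounding (linear, 186 patients), stepwise coverage was 94.5%.

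**The case against.** The strongest reply is that the size of the harm is assumed. The article gives neither confounder strengths nor an entry threshold, and a fuller analysis plan could set a loose one. At p<0.20, with no real confounding, or with strong confounders at 712 patients, stepwise selection comes close to the full model. This stands, and it is why the point says that selection can omit confounders and tends to narrow the interval, not that it must. It does not rescue the rule: the article fixes stepwise selection itself, and that rule performs at best about as well as keeping the listed covariates.

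A second reply concerns PEI. A reader might infer that the PEI aim is left without a valid estimate. The article does not support that. Outcomes promises the association of every recorded variable with each outcome, and lists factors associated with chemotherapy received as a secondary outcome. PEI is among the recorded variables. What is not assured is an adjusted PEI estimate. Nor is it a fault that PEI sits beside malnutrition in this model: the model targets malnutrition, PEI is plausibly upstream, and the article nowhere presents its coefficient as PEI's total association.

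A third reply is that eight covariates, several with more than two levels, may strain a logistic model at 186 patients. With 12 covariate terms at that size, the full model still covered 93.2%, against 86.8% for stepwise. The expected number of patients below 80% is not given, so sparse categories remain a practical concern.

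**Conclusion.** The point holds as a weakness of the adjusted models. Under moderate confounding and entry at p<0.05, coverage of the nominal 95% CI falls to roughly 77-89% at 186 patients and 81-92% at 326, and lower in the harshest linear settings. With all eight covariates kept it is about 95%. At 712 patients the bias is much smaller, though coverage still ranges from 78% to 94% with confounder strength.

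Two limits apply. The unadjusted t-test or rank-sum comparison of well-nourished and malnourished patients does not depend on selection and is untouched. A reader might also infer that the adjusted effect will be exaggerated. The simulations show this only because all confounders were set to act in one direction. In general the estimate moves toward the crude association, whichever way that lies.

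**What to change.** Delete the stepwise sentence. State that age, sex, race, ECOG status, tumor site, tumor stage, PEI and diabetes are all fitted, with malnutrition always included, in both the logistic and the linear model. If stepwise selection is kept at all, label it a sensitivity analysis. If any listed covariate is thought to lie on the path from malnutrition to dose delivered, justify its inclusion in advance.

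The cost is one sentence and a few degrees of freedom. No new data are needed and the stated sample sizes do not change. At 186 patients, sparse levels of race, ECOG, site or stage may need collapsing in the logistic model, preferably by a rule written beforehand.
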